### Methods of data collection

5.4

The source and timing of measures are summarized in Table 1. In accordance with the proposed research objectives, the outcome measures that will be performed are the following.

**TABLE 1 bco2313-tbl-0001:** Source and timing of variables obtained for the study.

Variable	Method of obtention	Data collection format	Source	Timing			
				Baseline	4 weeks	Up 6 months AFUV	Close‐out
Baseline data (sociodemographic, clinical, and life habits)	Personal interview/PCDN	Paper/electronic	P and HP	X			
Magnitude of infection	Urine culture/PCDN	Paper/electronic	Microbiology laboratory	X	X		
Rate of infection (asymptomatic and symptomatic UTI)	Urine culture/PCDN	Paper/electronic	Microbiology laboratory	X	X		
Adverse events during catheter insertion	Observation/PCDN	Paper/electronic	HP	X			
Adverse events during catheterization time	ID/PCDN	Paper/electronic	P		X		
Catheter biofilm	Viable cells counting/PCDN	Paper/electronic	Microbiology laboratory		X		
Antibiotic treatments related to catheterization	ID/PCDN	Paper/electronic	P and HP		X		
Healthcare resources utilization	ID/PCDN	Paper/electronic	P and HP		X		
Quantitative data for QoL and catheter satisfaction	Patients' questionnaire and EuroQoL 5D questionnaire	Paper/electronic	P	X	X		
Qualitative findings for acceptability and experience	Discussion groups	Audio recording	P			X	
Catheter opinion (professionals)	Professional questionnaire	Paper/electronic	HP				X
Workload perceived	NASA‐TLX questionnaire	Paper/electronic	HP				X

Abbreviations: AFUV, after follow‐up visit; EuroQoL 5D, EuroQol questionnaire—five dimensions—five levels; HP, health professional; ID, incident diary; NASA‐TLX, NASA Task Load Index questionnaire; P, participant/relative, friend, or informal carer‐completed questionnaire; PCDN, Patient Clinical Data Notebook; QoL, quality of life perceived; UTI, urinary tract infections.

#### Primary outcomes

5.4.1

##### Acceptability of the T‐Control device as well as the patient experience framed within the course of the disease; identification of the preferences and needs for training and information for use of the device and possible future improvements for the T‐Control device

The discussion group technique will be used in order to identify the discrepancies or affinities that exist in the participants' discourses, and therefore, it will be very useful to identify the aspects that the participants consider most and least beneficial based on their experience. The discussion groups will be moderated by a researcher with experience in this field who does not have a therapeutic relationship with the participants, thus allowing the free expression of their opinions. The discussion groups will be recorded with a voice recorder (and if the participants approve it, also in visual support to be able to analyse the non‐verbal language in more detail) and will be transcribed in its entirety verbatim for later analysis. For the analysis of the information, not only what is said but also the sounds and paralinguistic elements of the language will be considered, in order to collect the contextual information in which the opinions are expressed. The analysis of the information will be carried out concomitantly with its collection (from the narratives collected in the recordings) through axial coding because the categories, subcategories, and families of codes will be related to each other in order to find the relationships between the categories, their properties, and their dimensions. A software will be used for the qualitative analysis of narrative data to help in coding the data and relating codes with other properties, both numerical and categorical. The criteria of investigator triangulation, credibility, and transferability will be applied in order to ensure the validity of the data obtained.

##### Self‐perceived health‐related quality of life

The following instruments are administered to patients:
EQ‐5D‐5L^27^: This is a generic health‐related quality of life questionnaire that evaluates five domains: mobility, self‐care, usual activity, pain/discomfort, and anxiety/depression. Each domain is scored on a 5‐point scale, which yields a descriptive system that can be combined into a five‐digit number reporting the patient's state of health. Each EQ‐5D‐5L health state can be converted to a single summary index by applying a formula that attaches weights to each level in each dimension. A number of formulae or value sets are available for different countries, based on the valuation of EQ‐5D health states from general population samples. In this study, the value set estimated for Spain by Ramos‐Goñi et al.^28^ will be used. After applying these weights, the range of the summary index is 1 (perfect health) to 0 (health state equivalent to death). Negative values represent health states considered to be worse than death. The questionnaire also includes a visual analogue scale where responders are asked to indicate their health status on the day of the interview, ranging from 0 (worst possible health) to 100 (best possible health).Catheter‐related quality of life questionnaire: To evaluate the specific health‐related quality of life for long‐term catheterized patients, Rethink Medical has developed two specific instruments created in the context of this project based on the experience of our previous studies (Patient's workshop).^25^ The first one (Data S5), administered during the initial visit, consists of 47 questions, related to the patient's experience and journey with catheterization before the study, as baseline data. The questions are related to the type of catheter and accessories used, the experience of catheterization, emotions felt at the beginning (right from the moment of the prescription), satisfaction and comfort with the catheter, complications associated with catheter use, usability and complications associated with accessories and changes in the personal habits caused by the catheter's use, and how these issues have affected their lives. The second one (Data S6), administered during the follow‐up visit, consists of the same questions as the first one (but referred to the catheter and accessories used during the study) plus four questions related to information received when catheterized for the first time (total 51 questions). In order to quantitatively evaluate the answers, statements will include single answers with scores on a scale from 0 to 10, 0 to 5, and 0 to 4 for both questionnaires. The questionnaire devised by Rethink Medical is expected to be validated during the clinical study in conjunction with another study specially designed for its validation.

#### Secondary outcomes

5.4.2

##### Magnitude of infections

The magnitude of infection will be obtained from the analysis of urine culture samples taken from patients twice, during inclusion (time 0) and during withdrawal of the catheter (time 4 weeks; Table 1). In the event that the patient is prescribed an antibiotic for a UTI before the 28th day, the magnitude of infection will be evaluated at the time of prescription, through the analysis of a urine culture sample, according to usual clinical practice. The research staff will take between 5 and 10 mL of urine sample in a sterile container which will be transported to the laboratory in the shortest time possible (<2 h). If the transport or processing cannot be performed immediately, the sample will be refrigerated between 2°C and 8°C without exceeding 24 h until processing. The second urine sample will be collected from the new catheter inserted at the follow‐up visit. After seeding the urine in specific culture media, the microorganisms that have grown in the culture will be analysed to determine the number and type of microorganisms present using techniques based on biochemical tests and Matrix‐Assisted Laser Desorption/Ionization Time‐Of‐Flight (MALDI‐TOF) type mass spectrometry.

##### Rate of symptomatic and asymptomatic infections

The magnitude of infection obtained from the urine samples will be classified according to the following criteria based on the European Association of Urology (EAU) clinical guidelines^29^:
Symptomatic infection: The presence of pathogenic microorganisms in amounts greater or equal to 1000 Colony Forming Units/mL (CFU/mL) accompanied with symptoms will determine the existence of the infection.Asymptomatic infection: In the absence of infection symptoms, a quantity of microorganisms greater than or equal to 100 000 CFU/mL will indicate asymptomatic infection.

In addition to the presence or absence of infections to assess their rate, this variable will also be collected using the outcome measure “infection‐free days” (with a maximum possible value of 28 days) to be compared between Foley‐type catheters and T‐Control. Suppose the patient at some point prior to the follow‐up visit presents symptoms compatible with UTI. In that case, a urine culture will be performed to confirm the presence or absence of urinary infection, according to usual clinical practice. In the event that the patient receives an antibiotic for a UTI while he/she takes part in the study prior to the follow‐up visit, this will be recorded in the medical record. However, the patient will also be asked about it at the follow‐up visit when he hands in his/her incident diary, and this will be counted as an infection.

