## ENDPOINTS

3

The general purpose of this study is to determine the effectiveness, comfort, and experience of the patient catheterized with T‐Control® compared with patients with a conventional Foley catheter, by evaluating patients with long‐term urinary catheters.

Primary endpoints are as follows:
To analyse, through qualitative techniques, the comfort and acceptability of the T‐Control® device for the patient framed in the course of the disease, identifying preferences and training and information needs for the use of the device; andTo analyse and compare the degree of satisfaction and levels of self‐perceived health‐related quality of life of patients with both types of catheters.

Secondary endpoints are as follows:
To assess the preliminary effectiveness of T‐Control versus a common Foley catheter, by comparing the magnitude and rate of infections (both symptomatic and asymptomatic) due to the catheter among long‐term catheterized patients. Additionally, evaluate the effectiveness of T‐Control by comparing the days free of infection on the 28th day after catheterization;To compare the indication of antibiotic treatments associated with catheter use between the conventional Foley‐type catheter and the T‐Control device;To determine the biofilm formed in the catheters and identify the microorganisms that form this to evaluate its relationship with the onset of symptomatic and asymptomatic infections as well as different adverse events;To compare the number and relevance of adverse events related to bladder catheterization between T‐Control and the traditional Foley catheter;To assess the preliminary cost‐effectiveness of T‐Control versus the traditional Foley catheter from the public healthcare services perspective; andTo measure and compare the level of satisfaction and workload perceived of health professionals with both types of catheterization by means of a questionnaire at the end of the study.

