## ELIGIBILITY CRITERIA

4

Patient inclusion criteria are as follows: (1) men or women aged >18 years; (2) patients who require a change of bladder catheter; (3) absence of symptoms compatible with infection; (4) indication of bladder catheterization for 4 weeks; (5) maintained cognitive and physical capacity for self‐monitoring of the catheter valve; and (6) signed consent agreement.

Patient exclusion criteria are as follows: (1) symptoms of current UTI; (2) use of current antibiotic treatment or in the 2 weeks prior to inclusion in the study; (3) patients with malformations in the urinary tract; (4) immunocompromised patients; (5) patients with urological cancer; (6) patients who require continuous urine drainage (in the case of patients in the study arm) or hourly urine output measurement; (7) catheter insertion requiring more than one attempt; and (8) inability to read and understand Spanish.

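### The asymptomatic-infection rule ignores the time-0 culture, so bacteriuria that predates the study catheter counts as a week-4 infection and the endpoint measures day-28 prevalence

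*Protocol article*

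**What the plan says.** All references are to the protocol article.

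- **Entry (section 4).** The trial takes "patients who require a change of bladder catheter", so participants arrive already catheterised. The inclusion criterion on infection is "absence of symptoms compatible with infection". The related exclusions are "symptoms of current UTI; (2) use of current antibiotic treatment or in the 2 weeks prior to inclusion in the study". No culture result enters eligibility.
- **Sampling (section 5.4.2, Magnitude of infections).** Apart from cultures prompted by symptoms or treatment, urine is "taken from patients twice, during inclusion (time 0) and during withdrawal of the catheter". Each culture gives a count and a species identification. Table 1 lists both magnitude and rate of infection at baseline and at 4 weeks.
- **Case definition (section 5.4.2, Rate of symptomatic and asymptomatic infections).** With symptoms, the threshold is 1000 CFU/mL. For asymptomatic infection the rule is "In the absence of infection symptoms, a quantity of microorganisms greater than or equal to" 100 000 CFU/mL. Neither definition asks for a negative time-0 culture, a new species or a rise in count.
- **Infection-free days (same section).** The maximum is 28. Nothing is said about a patient who already meets the asymptomatic threshold at time 0.
- **Objective (section 3).** The comparison is of symptomatic and asymptomatic infections "due to the catheter among" long-term catheterised patients.

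**The concern.** A patient can enter without symptoms, with a count at or above the asymptomatic threshold, and leave at week 4 with the same organism at the same count. The definition makes that patient a week-4 infection. The organism was there before the study catheter was inserted, so the case cannot support a statement that the infection arose from it.

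Two consequences follow. Patients already positive at time 0 cannot contribute a first positive culture, so any effect of the device on new infection shrinks in the all-patient comparison. And with 25 patients per arm, carriage at entry will differ between arms by chance, and part of that difference passes into the week-4 result unless the analysis uses the time-0 culture. The Discussion names infection as one of the most important data items of the study, so the meaning of this endpoint matters even though it is secondary.

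**Working it through.** **Figure in the plan.** None is given for infection: no carriage, persistence or incidence rate. The only sample size, 25 per group, is for quality of life. It reproduces with a t-test at a standardised difference of 0.95, two-sided alpha 2.5% and an assumed 80% power: 22.4, so 23 per group, and 23 / 0.95 = 24.2, so 25. It serves here only as the number per arm.

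**Assumptions (not in the documents).** Baseline positivity p0 is 30, 50, 70 or 90%. Persistence to week 4 is 90% in both arms. The risk of new infection among baseline-negative patients is 40% with Foley and 20% with T-Control.

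**Step 1: what the rule as written observes.** Week-4 prevalence = 0.9 × p0 + (1 − p0) × new-infection risk.

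| p0 | Foley | T-Control | Difference | Ratio | Baseline-negative per arm, 25 × (1 − p0) |
|---|---|---|---|---|---|
| 30% | 0.27 + 0.28 = 55% | 0.27 + 0.14 = 41% | 14 points | 0.75 | 17.5 |
| 50% | 0.45 + 0.20 = 65% | 0.45 + 0.10 = 55% | 10 points | 0.85 | 12.5 |
| 70% | 0.63 + 0.12 = 75% | 0.63 + 0.06 = 69% | 6 points | 0.92 | 7.5 |
| 90% | 0.81 + 0.04 = 85% | 0.81 + 0.02 = 83% | 2 points | 0.98 | 2.5 |

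With equal persistence in both arms, the difference is (1 − p0) × 20 points. Among baseline-negative patients it remains 20 points (ratio 0.50).

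**Step 2: chance imbalance in carriage.** The between-arm difference in baseline positivity has SD √(2 × p0(1 − p0) / 25): 14.1 points at p0 = 50% and 8.5 points at 90%. Only part of this reaches the endpoint, because one more carrier raises the expected week-4 count by 0.9 minus the new-infection risk: 0.5 with Foley and 0.7 with T-Control. The contribution is therefore √((0.5² + 0.7²) × p0(1 − p0) / 25) = √(0.74 × p0(1 − p0) / 25):

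- p0 = 50%: √(0.74 × 0.25 / 25) = 8.6 points
- p0 = 90%: √(0.74 × 0.09 / 25) = 5.2 points

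**Step 3: set against total sampling error.** The SD of the observed difference is √((q₁(1 − q₁) + q₂(1 − q₂)) / 25), with q₁ and q₂ the week-4 prevalences from step 1:

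- p0 = 50%: √((0.2275 + 0.2475) / 25) = 13.8 points
- p0 = 90%: √((0.1275 + 0.1411) / 25) = 10.4 points

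The step 2 contributions are components of these totals, not additions. As shares of variance they are 0.0074 / 0.0190 = 39% and 0.00266 / 0.01074 = 25%.

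**The case against.** **The text gives thresholds for a sample, not an analysis rule.** Table 1 classifies infection at both times, and the objective's reference to the catheter could be read as requiring attribution. An SAP is promised and is not shown. It is true that the SAP could specify baseline adjustment, and the absence of an adjusted model here is not a finding. The chi-square and t-test sentence in section 5.7 reads as a check of group comparability, so it does not fix an unadjusted infection analysis either. What remains is that the case definition and the attribution are both stated in this document and do not match. Adjustment alone would not turn a persisting organism into an infection arising on the study catheter.

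**Day-28 prevalence is a valid randomised comparison.** This stands. A reader might infer that the rule biases the result towards one arm. It does not: randomisation balances carriage in expectation.

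**The device might also clear or reduce existing bacteriuria.** The background offers valve-regulated flushing and slower biofilm growth as mechanisms. A reader might infer that every device effect is diluted. The calculation shows dilution only of an effect confined to new infection, because it sets persistence equal in both arms. This is also why the all-patient comparison is worth keeping.

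**The gain is modest.** This also stands. Take 40% vs 20% new-infection risk, two-sided alpha 0.05, and every carrier staying positive. Power as written is 0.20 at 20% carriage and 0.06 at 80%. For new infection in baseline-negative patients it is 0.28 and 0.10. Neither is adequate. The case for change is interpretability more than power.

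**Infection-free days may not be affected.** The surrounding text concerns symptom-triggered cultures and antibiotic prescriptions. If the measure counts only those, every entrant is infection-free on day 0. A reader might infer that the measure fails in the same way, but that follows only if it includes asymptomatic infection, which the text leaves open.

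**Conclusion.** The point holds for the asymptomatic component. Entry by symptoms, a count-only definition and attribution to the catheter together mean that persisting bacteriuria counts as a week-4 infection, and the endpoint is prevalence at day 28.

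Under the stated assumptions, a 20-point effect on new infection appears as 14 points at 30% baseline positivity and as 2 points at 90%. The size rests on carriage, persistence and incidence rates that the documents do not give. That pre-existing cases are counted follows from the text alone, whatever those rates are.

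It would be tempting to say that the full 8.5 to 14 point imbalance in carriage passes into the endpoint. It does not. About 5 points (at 90%) to 9 points (at 50%) does, as part of ordinary sampling error. That part is avoidable because the time-0 culture is already collected.

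The endpoint is secondary, in a pilot sized on quality of life, so this is a correction to make before data lock and not a threat to the primary comparison.

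**What to change.** 1. Keep the week-4 comparison in all patients, name it as prevalence at day 28, and adjust for or stratify by time-0 culture status.
2. Define new infection for a separate report: threshold met at week 4 in a patient below it at time 0, or by a species that was not at threshold at time 0. Report persistence in baseline-positive patients alongside it.
3. Base any statement that infections are due to the catheter on new infection.
4. State what infection-free days count. If asymptomatic infection is included, score them in baseline-negative patients only. Otherwise state that they count symptomatic or treated infection.

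The cost is wording and analysis time. Counts and species are already obtained at both visits, so no samples are added. The drawback is that few patients are at risk for the new-infection comparison, about 3 to 18 baseline-negative patients per arm over the assumed range. Its interval will be wide and should be reported as such.

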#### Criteria for discontinuing or modifying allocated interventions

5.2.1

Reasons for going off or discontinuing the trial are as follows:
Adverse events that may compromise the patient's safety;Need for antibiotic treatment for a reason unrelated to the use of a bladder catheter;The patient's refusal to continue (in the event that, according to clinical practice, they still needed to carry an indwelling bladder catheter, the T‐Control catheter would be exchanged for the conventional Foley‐type catheter); andDeath.

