##### Number of adverse events related to catheterization

The type and number of adverse events will be registered in the Patient's Clinical Data Notebook: accidental disconnection of the catheter, obstruction, pain, loss of urine per catheter, haematuria, and accidental spills caused by the professional during insertion. The patient will receive a Patient Incident Diary to write down the incidents, along with other information that may be of interest during catheterization. Timing and source of adverse events data are summarized in Table 1.

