### Analysis plan

5.7

A statistical analysis plan will document the scheduled analysis, to be finalized before the data lock. The final analysis will take place after full recruitment and follow‐up, at the end of the study.

The analysis population will consist of all patients who meet the selection criteria and are randomized. All patients included in the study and excluded from the analysis will be listed along with their reason for exclusion. Additionally, additional analysis will be performed on patients who complete 4 weeks with the catheter. Subjects who withdraw from the study for any reason after signing the informed consent will not be replaced. No imputation will be made for missing data.

Descriptive statistics will be carried out on the variables under study, using frequencies and percentages for qualitative variables and mean with standard deviation for quantitative variables that follow a normal distribution; otherwise, the median and interquartile ranges will be calculated.

A bivariate analysis will be carried out between the control–study groups with respect to the independent variables to know the comparability of the groups using the Chi square tests for qualitative variables and for the quantitative variables *t*‐Student or Mann–Whitney U, depending on the normality of the sample. All are under a 95% confidence interval and considering statistically significant results with a *p*‐value < 0.005.

In the event that the results are discordant, deviations and/or violations of the protocol will be analysed. For all analyses, the SPSS 24.0 statistical package^31^ will be used and will be carried out by a person who will not know if the patients have been in the intervention or control group.

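### Infection-free days and adverse-event numbers are set as raw counts over a nominal 28 days, with no allowance for catheters removed early (minor)

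*Protocol article*

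**What the plan says.** **Infection-free days.** Section 3 (Endpoints) evaluates effectiveness by "comparing the days free of infection on the 28th day after catheterization". Section 5.4.2 (Rate of symptomatic and asymptomatic infections) makes this a count of days, "with a maximum possible value of 28 days) to be compared between" Foley-type catheters and T-Control. An antibiotic given for a urinary infection before the follow-up visit counts as an infection.

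**Adverse events.** The objective in section 3 is "To compare the number and relevance of adverse events related to bladder catheterization between" the two catheters. Section 5.4.2 adds: "The type and number of adverse events will be registered in the" Patient's Clinical Data Notebook. No denominator of catheter-days is mentioned.

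**Early exit.** Section 5.2.1 opens its list with "Reasons for going off or discontinuing the trial are as follows". The reasons are adverse events that may compromise safety, "Need for antibiotic treatment for a reason unrelated to the use of a bladder catheter", refusal, and death.

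**Analysis.** Section 5.7 takes all eligible randomised patients as the analysis population and says "No imputation will be made for missing data". It adds an analysis of patients who complete 4 weeks with the catheter. Section 5.6 puts early terminators into a substudy analysis. A separate statistical analysis plan is announced in section 5.7 and is not shown. The planned dropout in section 5.3 is 5%.

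**The concern.** A count capped at 28 days measures infection-free time only if every patient is observed for 28 days or until infection. The article itself provides for patients who are not. An uninfected patient who leaves on day 8 can be handled in three ways:

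- **Scored to exit:** the value is 8, the same as for a patient infected on day 8.
- **Treated as missing:** with no imputation the patient drops out of this comparison, while patients infected before leaving keep their low values.
- **Credited with 28:** about 20 unobserved days count as infection-free.

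None of the three reflects time actually observed. The first two lower the mean in the arm with more early exits, and the third raises it. The adverse-event number has a parallel problem, since a catheter worn for fewer days has fewer days in which events can occur.

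If early stopping differed between arms, a difference could appear on either endpoint with no true difference behind it. The trial is open-label, so unequal stopping is possible.

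**Working it through.** **Plan's own figure.** The article gives none for these two endpoints. Its one calculation, 25 per group in section 5.3, concerns the quality-of-life endpoint. It reproduces at 2.5% two-sided, standardised difference 0.95 and an assumed 80% power (power is not stated): the t-test needs 22.4, so 23, and 23/0.95 = 24.2, so 25. Only its 5% dropout is used below.

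**Assumptions (not in the documents).** Infection risk by day 28 is 30% in both arms, with constant hazard. There is one adverse event per 28 catheter-days in both arms. Early leavers exit uniformly between days 1 and 28, independently of infection and events.

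**Infection-free days, scored to exit**

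- Daily hazard λ = −ln(0.70)/28 = 0.01274.
- True mean to day 28 = (1 − 0.70)/λ = 0.30/0.01274 = 23.55 days.
- For a leaver with exit day W, the expected score is (1 − E[exp(−λW)])/λ. Here E[exp(−λW)] = (exp(−λ) − exp(−28λ))/(27λ) = 0.835, which gives 12.92 days.
- Each leaver therefore costs on average 23.55 − 12.92 = 10.63 days.
- 5% leavers: 23.55 − 0.05 × 10.63 = 23.02, a loss of about 0.5 day.
- 20% leavers: 23.55 − 0.20 × 10.63 = 21.42.
- Gap at 20% v 5%: 23.02 − 21.42 = 1.60 days.

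**The same 20% v 5% under the other two rules**

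- A leaver is infected before exit with probability 1 − 0.835 = 0.165. These infections contribute E[T; T<W] = 12.92 − E[W·exp(−λW)] = 12.92 − 11.47 = 1.45 days per leaver.
- Uninfected leavers missing: (0.80 × 23.55 + 0.20 × 1.45)/(0.80 + 0.20 × 0.165) = 22.97, against (0.95 × 23.55 + 0.05 × 1.45)/(0.95 + 0.05 × 0.165) = 23.42. The gap is about 0.5 day against the arm that stops more.
- Uninfected leavers credited with 28: a leaver averages 1.45 + 0.835 × 28 = 24.84, so the means are 0.80 × 23.55 + 0.20 × 24.84 = 23.81 and 0.95 × 23.55 + 0.05 × 24.84 = 23.62. The gap is about 0.2 day in favour of the arm that stops more.

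Both the size and the sign of the artefact therefore depend on the unstated rule.

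**Adverse events.** Mean wear of a leaver is (1 + 28)/2 = 14.5 days. Relative exposure is 0.95 + 0.05 × 14.5/28 = 0.976 at 5% leavers and 0.80 + 0.20 × 14.5/28 = 0.904 at 20%. The ratio is 0.904/0.976 = 0.926, or about 7% fewer events.

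**Simulation with no true difference** (25 per arm, 3,000 runs, days scored to exit, Mann–Whitney at 5%):

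| Early stopping | Mean infection-free days | Events per patient | Events per 28 catheter-days | False positives (days) |
|---|---|---|---|---|
| 5% v 5% | 23.00 v 23.06 | 0.98 v 0.98 | 1.00 v 1.00 | 4.6% |
| 20% v 5% | 21.45 v 23.01 | 0.91 v 0.98 | 1.00 v 1.00 | 11% |
| 40% v 5% | 19.29 v 23.04 | 0.80 v 0.97 | 1.00 v 1.00 | 38% |

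The simulated means agree with the formulas. Expressing events per catheter-day removes the artefact in every row.

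**The case against.** **It belongs to the statistical analysis plan.** Scoring of early leavers, censoring and exposure offsets are commonly settled there, and section 5.4 describes data collection. Recording a number does not prevent reporting a rate. This stands in part: the unseen plan may supply the rule. But the article has already fixed the scale, the population and the absence of imputation, and under those three choices a day count cannot reflect wear time.

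**Wear time is addressed elsewhere.** The 4-week completer analysis does equalise wear time, so it would be wrong to infer that the article ignores the matter. That analysis is only additional, however, and it selects patients on something that happens after randomisation. The substudy of early terminators sets no scoring rule.

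**Stronger readings.** A reader might infer that an uninfected early leaver is scored as infected. Section 5.4.2 does not say so; that is one of three possibilities. A reader might also infer that the arm with more stopping will look safer. That holds only for later events that are never observed: a patient who stops because of an adverse event already has that event counted, and spills during insertion do not depend on wear. Nor do the documents show that stopping will be more frequent with T-Control. The exchange to Foley in section 5.2.1 says what follows a refusal, not how often refusals occur.

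**Size.** At the planned 5% dropout, about one patient per arm, little happens. This stands.

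**Limits of a time-to-event analysis.** Asymptomatic infection is normally found only by the week-4 culture, so its onset is unknown, and censoring at removal is informative when the patient stops because of the catheter. Both points stand and shape the fix.

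**Conclusion.** The point holds as a minor one. The two endpoints are raw counts over a nominal 28 days, patients may leave earlier, and no stated rule makes the counts reflect time observed. With 5% stopping in both arms, the loss is about 0.5 day (scored to exit) and 2% of events, with no bias between arms. Bias requires unequal stopping, for which the documents give no figure. At an assumed 20% v 5%, the spurious gap is about 1.6 days if days are scored to exit, 0.5 day if uninfected leavers are missing, and 0.2 day in the opposite direction if they are credited with 28. The same arm shows about 7% fewer adverse events. False positives on infection-free days reach about 11% under scoring to exit. These sizes rest on the assumed 30% infection risk, constant hazards and exits unrelated to outcome. The endpoints are secondary, in a 50-patient pilot whose effectiveness assessment is called preliminary, so the primary conclusions are not touched.

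**What to change.** - **Symptomatic or antibiotic-treated infection:** analyse time from insertion to first infection, censored at removal of the study catheter. Compare arms by log-rank test or by restricted mean infection-free time to day 28, which keeps the result in days. Add a sensitivity analysis that treats catheter-related stopping as a competing event.
- **Asymptomatic infection:** keep it as a yes/no result at the removal culture, because its onset date is unknown.
- **Adverse events:** report those in the catheter period per 100 catheter-days, for example by Poisson regression with log catheter-days as offset. Report insertion events per insertion.
- **Completer analysis:** keep it as supportive only.

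The cost is a change of analysis wording and slightly more analysis work. Sample size and visits do not change. The method relies on recorded removal and event dates. The diary form is not shown, so it should be checked that these dates are captured for every patient, including early leavers.
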